**Figure 2 f2:**
[figure not shown]
A schematic view of intervention delivery at Chennai, Gujarat, and Ibadan. There are three schools (A, B, C) per site; universal assessments are conducted at four time-points (baseline, 8 months, 15 months, 22 months); dark green box represents delivery of universal health literacy; light green box represents delivery of counselling intervention.

The intervention will be delivered in two stages: (1) all adolescents in the intervention school will receive the health literacy component (dark green box); (2) a subset of adolescents in the intervention school will receive the counselling component if they meet the pre-defined threshold indicating nutritional/weight and/or mental health problems (light green box). These adolescents will comprise the sub-cohort who will be followed up at two/three and 12 months. Once the counsellors are introduced into each school, they will remain for the duration of the study.

Each study site will have three schools (school A, B and C) who will receive the intervention in a staggered manner so that each of the three schools will eventually receive the intervention. Schools will initially serve as the control condition and then incrementally transition to the intervention phase. Therefore, while schools function as the control condition at specific time points, there are no fixed “control schools.” We do not consider contamination to be an issue in this design because students will not switch schools, and counsellors are assigned to a school each.

In intervention schools, children identified with mental or physical health challenges will be referred for further evaluation and care by the school counsellor, with support from the school point of contact. In schools that are still in the control condition, information about children with identified mental or physical health challenges will be shared with the school point of contact, who will inform family members as needed and provide signposting advice (e.g., posters and announcements about local services and helplines). All adolescents in the intervention and control conditions will complete the baseline universal assessments prior to roll-out of the intervention. Adolescents in the sub-cohort will complete targeted assessments (**Table 2**) at baseline, two/three and 12-month follow-up. All selected schools are publicly funded and run by the Government. We will provide training to teachers within the selected schools (e.g., identification of symptoms and referral pathways).

**Table 2 T2:** Targeted assessments administered to cohort of adolescents receiving school counselling support.

Name	Description	Items in scale	Time-points
Patient Health Questionnaire (PHQ-9)	Validated depression scale	• Little interest or pleasure • Feeling down/hopeless • Trouble sleeping • Feeling tired • Poor appetite/overeating • Feeling bad about self • Trouble concentrating • Moving/speaking slowly • Thoughts be better off dead	Baseline, 2 and 12 months
Generalised Anxiety Disorder scale-7 (GAD-7)	Validated scale for anxiety symptoms	• Feeling afraid • Becoming annoyed/irritable • Being restless • Trouble relaxing • Worrying too much • Not able to stop/control worry • Feeling nervous/anxious	Baseline, 2 and 12 months
Childrens Global Assessment Scale (C-GAS)	Validated scale for adolescent functioning	General functioning is assessed based on information from previous assessments and interviews with the child, their parents, carers, and school.	Baseline, 2 and 12 months
The SDQ follow-up questions	Questions to address whether intervention has helped mental and behavioural health	• Has the intervention reduced problems? • Has the intervention helped in other ways, e.g. making the problems more bearable?	2 and 12 months
Physical health and diet questions (selected from existing scales)	Bespoke questions to address whether intervention has helped physical health and diet (items taken from validated scales)	Example items: • Exercise can help me reduce my stress level • I know what healthy food products are • If I eat five or more fruit/veg a day, I will feel good about myself	2 and 12 months

School counsellors will be responsible for delivering all stages of the intervention, with some assistance from project experts in Ibadan. We will ensure that elements of the study (including assessments and intervention modules) are tailored to routine school activities where possible to minimise burden on schools and maximise implementation success (e.g., some health literacy modules will be presented during assembly, weight measurements will be taken as part of school’s regular health monitoring schedule). There will be some flexibility incorporated into individual site timelines to account for variations in holidays and exam periods (as discussed with stakeholders during the development work).

### Participants and recruitment

We will recruit adolescents from three schools per site (total = nine schools). The inclusion criteria are: (1) being a school going adolescent aged 12–18 years; and (2) willing to take part in the mental and physical health assessments. We will recruit approximately 200 adolescents per school, equalling 600 adolescents per site, and 1, 800 adolescents in total. In India, adolescents will be recruited from grades 6 to 8. Pilot work in Chennai and Gujarat indicates that this will equal approximately 200 adolescents per school. In Ibadan, adolescents will be recruited using stratified random sampling to reach the sample target number. Sites will continually monitor intervention roll out to allow improvements to be incorporated in real-time. Implementation strategies will include providing ongoing training and supervision for counsellors, local consensus discussions and educational meetings, creating a learning collaborative approach to capture and share local knowledge, and auditing the implementation processes to enhance participation and maintenance.

### Phase 3: post-intervention phase

Assessments conducted at the post intervention phase include: (a) evaluation of the implementation process; (b) impacts of the health literacy and counselling components of the intervention; and (c) health economic evaluation.

### Evaluation of implementation process

Guided by the Consolidated Framework of Implementation Research (CFIR) (31), we will assess a comprehensive range of implementation outcomes using both quantitative and qualitative tools (32). Our primary quantitative outcomes (**Table 3**) are acceptability and appropriateness, which we will assess using published scales (e.g., Acceptability of Intervention Measure) and screening forms (e.g., percentage of teachers trained, percentage of adolescents engaging with the intervention). Secondary quantitative outcomes include fidelity, adoption and sustainability which will be assessed with published scales (e.g., NoMAD instrument) and screening forms (e.g., percentage delivery and adherence, number of sites continuing the intervention). We will also assess implementation outcomes at the school (e.g., reach and equity) and individual (e.g., adolescent satisfaction) level including whether there are differences in implementation outcomes based on gender and other social determinants.

**Table 3 T3:** Main quantitative implementation outcomes.

Implementation outcome	Description	Published scales	Screening forms
Acceptability	Is the intervention acceptable in terms of content, delivery, complexity and credibility	Acceptability of Intervention Measure (AIM) • Meets approval • Appealing to me • Likes • Welcome	• % Teachers trained in care pathway guidance • % Adolescent participation and engagement
Appropriateness	Is the intervention compatible with the setting and suitable for adolescents	Intervention Appropriateness Measure (IAM) • Seems fitting • Seems suitable • Seems applicable • Seems a good match	N/A
Fidelity	Was the intervention implemented as intended	N/A	• % Delivery and adherence to each component • Number of dropouts
Adoption	Extent of uptake of the intervention	Normalisation Measure Development Questionnaire (short NoMAD) Example items: • I can see the potential value of [the intervention] for my work • There are key people who drive [the intervention] delivery forward and get others involved	N/A
Sustainability	Intervention and the benefits it will generate are sustained overtime Extent to which adolescents who required specialist care continued treatment over time	Normalisation Measure Development Questionnaire (short NoMAD) Example items: • I will continue to support [the intervention]	• Number of sites that continue the intervention past the study • % sustained personalised treatments

Our quantitative assessments will be supplemented with in-depth qualitative interviews and focus groups with teachers, families, adolescents, counsellors, and policy makers. We will consider the impact of internal and external context on intervention development, delivery, and reception. External context might include factors such as government policy (or lack of), financial resource, workforce capability, and cultural assumptions (such as stigma and extended family ethos and support). Internal context could include factors such as leadership (e.g., accountability, influence), background of counsellors, knowledge exchange and capacity building, co-production and adaptation process, and plans for sustaining the intervention once funding ceases. We will also consider the impact of recipient characteristics such as gender (e.g., adolescent girls might not have the same access to food) and socioeconomic status (e.g., impact on health behaviours and outcomes). Qualitative data will be stored in a central depository to facilitate comparative analysis across sites.

### Health economic evaluation

Our health economic evaluation will estimate the resources required to implement the intervention. A bottom-up ingredients-based costing will be conducted to identify the additional resources required to deliver the intervention. Data will be collected retrospectively based on study records and using a costing spreadsheet designed specifically for the study. The local teams will assess the unit costs per activity of the key outputs of the intervention (e.g., number of students counselled). These costs will be presented alongside study outcomes in a cost-consequence analysis and, where appropriate, compared with key outcome measures in a cost-effectiveness analysis (33). We will conduct scenario and sensitivity analyses to illustrate how costs might be affected by implementation strategies, and the potential longer-term impacts beyond study follow-up.

### Analysis plan

We will conduct school-level and individual (cohort) level analysis. We will compare adolescents in the control and intervention schools to determine whether the health literacy intervention is associated with an increase in help-seeking. We will use non-randomised difference-in-difference (DID) analysis (34) to adjust for differences between schools (school-effects) and over time (time effects). The DID design is a quasi-experimental approach which enables the researcher to study causal relationships in settings where randomised control trials are unfeasible or unethical (35). Our outcomes are predominantly proportions (e.g., proportion seeking help), thus we will use a binomial-logistic regression model approach to estimate relative (odds ratios) and absolute (differences in proportions) effects of the intervention. The number of schools is likely too small to reliably estimate school-level random effects, so a mixed model is not considered. We will analyse our universal repeated assessments (administered to all adolescents in intervention and control schools) to determine the effects of the health literacy component on longitudinal mental and physical health measures (baseline, 8, 15, and 22 months). These data will be analysed using an individual level linear model with adolescent random effects, school, time and intervention fixed effects. We will conduct sub-analysis with the cohort of adolescents receiving counselling. The targeted cohort assessments (**Table 2**) will allow us to describe the trajectories of adolescents receiving the counselling component of the intervention to determine whether the counselling has an impact on mental and/or physical health outcomes. For the continuous cohort outcomes (“universal assessment”) the minimum detectable standardised effect size is approximately 0.1 assuming an individual autocorrelation coefficient between time periods of 0.8.

Our sample size calculation is based on the proportion of adolescents seeking help in the control versus intervention groups. While epidemiological findings from LMICs show that approximately 8-10% of youths experience mental health problems requiring intervention, less than 1% receive help (36, 37). Since we are signposting adolescents in the control schools to local services, we anticipate that approximately 5% might seek help. For those receiving the ISOBAR intervention, we predict an increase in the proportion of adolescents who seek care (among those who reach the pre-defined threshold) from 5% (in control arm) to 11-12% (in intervention arm). We are planning to recruit three schools per site. Our sample size calculation assumes an increase in help-seeking of 6-7% in the intervention group compared to the control schools (i.e., 5 to 11-12%). Thus, if we recruit 200 adolescents per school, we will have 80-90% power to detect an improvement of at least 6–7 percentage points. Therefore, we plan to recruit a minimum of 200 adolescents per school per site: 200 x 3 = 600 adolescents per site (Total n = 1,800).

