### Objectives, aims, and research questions

The main aim of ISOBAR is to develop and test the effectiveness and implementation of a school-based three-stage (assessment and referral, universal health literacy, and indicated counselling) composite physical and mental health intervention in India (Chennai and Gujarat) and Nigeria (Ibadan).

Key objectives include:

To co-develop and culturally adapt a universal health literacy intervention combining mental and physical health modules.To assess all adolescents for emotional, behavioural, and nutritional/weight problems using validated assessment tools.To develop, and culturally adapt, an indicated counselling intervention for adolescents reaching pre-determined thresholds on the above universal assessment indices.To implement and evaluate the school-based intervention at each site using quantitative and qualitative implementation assessment tools.To assess the costs of the intervention and explore how these relate to consequences and affordability.To estimate the effectiveness of the school-based intervention (health literacy and counselling components) with a suite of outcome measures, including help-seeking, mental health symptoms, diet and activity, and anthropometric measures.

We have two primary research questions:

Does a health literacy intervention (delivered to all adolescents at classroom level) increase help-seeking behaviours?Do adolescents who receive counselling for physical and/or mental health problems experience improved outcomes?

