#### (1) Universal assessment and referral

We selected assessment tools to measure mental health and behavioural problems (Strengths and Difficulties Questionnaire: SDQ; Global School-Based Student Health Survey: GSHS), well-being (WHO-5 well-being index), nutritional problems, and at-risk weight status (Body Mass Index: BMI) Tools selected were: (1) relatively quick to administer; (2) well-established; (3) previously used and validated in our study countries; and (4) available in the local language. We will also assess help-seeking behaviour and health literacy with bespoke scales. The health literacy scale will draw on the conceptual framework developed by Jorm (27) and capture key components of the intervention (e.g., beliefs about the utility of counselling, stigma surrounding mental illness). Assessment scales are self-report and will be completed by adolescents at baseline, 8, 15 and 22 months with support from trained research assistants. Weight, height and arm circumference measurements will be recorded by researchers. All adolescents (in control and intervention schools) will be assessed. Adolescents in the intervention school reaching the pre-determined threshold on either the SDQ and/or the BMI (**Table 1**) will be referred to the inhouse counselling intervention. Adolescents in the control schools who are identified through the universal assessments as having potential mental health or nutritional concerns will not be left without support. All participants with such concerns will be informed of their screening results in an age-appropriate manner. Where necessary, efforts will be made to inform parents or guardians through the school system, in line with ethical and safeguarding procedures. Participants and their families will be advised to seek appropriate care, and the research team will facilitate this by providing information on available services, including referral pathways to specialist mental health care.

**Table 1 T1:** Universal assessments administered to all adolescents in intervention and control schools.

Name of scale/assessment	Description	Items in scale	Threshold for referral to counsellor	Time-points
Socio-demographic questionnaire	Bespoke scale assessing key demographic factors (culturally adapted for each site)	Age, gender, religion, parents’ education level, family size and composition, geographical setting	N/A	Baseline

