Help-seeking behaviour questionnaire	Bespoke scale assessing help- seeking	Sought help in the past six months, frequency of help- seeking, and who from/what for	N/A	Baseline, 8, 15, 22 months
Health literacy	Bespoke scale based on Jorm (27) conceptual framework	Example items: Ability to give advice, how to improve well-being, thoughts on counselling, stigma, knowledge of mental illness	N/A	Baseline, 8, 15, 22 months
Strengths and Difficulties Questionnaire (SDQ)	Validated scale to assess emotional and behavioural issues	• Emotional symptoms • Conduct problems • Hyperactivity/inattention • Peer problems • Prosocial behaviour	• Based on algorithm (hierarchical): -Very high score/very high impact - High score/very high impact -Very high score/high impact -High score/high impact (Impact score is given more weight)	Baseline, 8, 15, 22 months
WHO-5 well-being index	Validated measure of well-being	• Cheerful/good spirits • Calm and relaxed • Active and vigorous • Fresh and rested • Things that interest me	N/A	Baseline, 8, 15, 22 months
Global School-Based Student Health Survey (GSHS)	Validated scale for adolescents to assess risks for morbidity and mortality	• Dietary behaviours • Drug use • Hygiene • Mental health • Physical activity • Sexual behaviours • Drug use • Tobacco use	N/A	Baseline, 8, 15, 22 months
Body Mass Index (BMI)	Screening tool for weight-related health risks	• Weight in kg • Height in metres^2^	Sites will follow country specific thresholds for overweight and obesity	Baseline, 8, 15, 22 months

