#### (3) Indicated counselling

All students identified as having serious or very high emotional or behavioural problems, with functional limitations as measured by the SDQ, and those children who did not screen positive on the SDQ but sought help, will be provided with in-school counselling within a month of the initial assessment. Sites are currently developing and piloting site-specific manuals to underpin the counselling component of the intervention. The manual will assist with the training of the counsellors and help ensure fidelity. Counsellors will be encouraged to develop a system of peer support across sites to facilitate mutual learning and enhance problem-solving skills. Counsellors will be trained to: (1) support young people with nutritional and/or mental health problems; (2) identify serious problems requiring specialist care and help young people to access that care; and (3) support teachers in schools to refer adolescents in need. Counsellors will use various techniques including problem-solving, active listening, and behaviour activation. Format and duration of counselling sessions will be tailored to adolescent need and severity of symptoms, with (one-to-one or group) sessions available for the duration of the project (or as needed) once the counselling is introduced into the intervention school). Adolescents will be referred for specialist care (e.g., psychiatric care) if there is no improvement during the counselling intervention period, or if the adolescent is demonstrating psychotic symptoms or suicidal ideation. Three counsellors per site will be recruited to deliver the intervention. Chennai and Gujarat will recruit graduates from mental health and social work fields as counsellors. Ibadan will recruit lay health workers due to a shortage of mental health professionals in the area.

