### Trajectories of adolescents receiving the counselling component

Adolescents forming the cohort referred to counselling will complete assessments at the start of the counselling sessions and at two/three- and 12-month follow-up. Assessments include the Patient Health Questionnaire-9 for depression (38), the Generalised Anxiety Disorder scale-7 (GAD-7) (39), the SDQ follow-up questions to assess the impact of the intervention (40) and the Childrens Global Assessment Scale to assess functioning (41). We will select suitable measures for adolescents receiving counselling for nutritional/weight problems (e.g., food frequency questionnaire, physical activity questionnaire (42)). We will also explore counsellors and adolescents’ experience of the intervention with one-to-one semi-structured interviews.

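### The second primary question rests on uncontrolled change in adolescents selected mainly by threshold, so the planned trajectories cannot show whether counselling has an effect

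*Protocol article*

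**What the plan says.** The section on objectives and research questions lists two primary questions. The second is: "Do adolescents who receive counselling for physical and/or mental health problems experience improved outcomes". The same section includes the counselling component in its effectiveness objective.

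The only analysis given for that question is in the Analysis plan, where the targeted cohort assessments are to "describe the trajectories of adolescents receiving the counselling component of the intervention to determine whether the counselling has an impact" on health outcomes. The caption of Table 2 shows who provides these data: "Targeted assessments administered to cohort of adolescents receiving school counselling support". The section on trajectories adds that this cohort "will complete assessments at the start of the counselling sessions and at two/three- and 12-month follow-up". The measures are PHQ-9, GAD-7, C-GAS, the SDQ follow-up questions and some physical health and diet items.

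The section on universal assessment and referral describes entry as "Adolescents in the intervention school reaching the pre-determined threshold on either the SDQ and/or the BMI". In Table 1 the SDQ rule takes the upper tail only: "Very high score/very high impact - High score/very high impact -Very high score/high impact -High score/high impact". The section on indicated counselling adds a second route, for "those children who did not screen positive on the SDQ but sought help".

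The controlled comparisons belong to the other primary question. The Analysis plan and the section on the effectiveness of the health literacy component assign both the intervention-versus-control comparison and the longitudinal model with school, time and intervention effects to health literacy. The universal measures are nevertheless collected everywhere: "All adolescents (in control and intervention schools) will be assessed". Table 1 schedules SDQ, WHO-5 and BMI at baseline, 8, 15 and 22 months.

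**The concern.** A group chosen because a score is high will on average score lower when measured again, treated or not. Some adolescents also recover unaided, all of them age and pass through school terms, and the crossed-over schools run the health literacy programme alongside counselling. A before-after description of the counselled group contains all of this and has no counterpart from which to subtract it.

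The article's caveats do not reach the problem. The Highlights and the Phase 2 section limit causal inference because roll-out is not randomised, and Phase 2 relies on school and time fixed effects. Those effects need untreated observations on the same measures, and the Table 2 measures have none. Regression to the mean, natural recovery and a comparator for this cohort are not mentioned.

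At stake is an answer to one of two primary questions that would credit counselling with change it may not have caused. That answer could then enter the cost-effectiveness work and the policy recommendations.

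**Working it through.** **The plan's own figure.** No detectable effect or power is stated for the counselling question. The nearest figure is the detectable effect of about 0.1 SD for the universal assessments at an individual autocorrelation of 0.8. It can be reproduced with school and time fixed effects, an adolescent random intercept, four periods and 200 adolescents per school. Assumptions added are one school crossing after each assessment, two-sided 5% and 80% power. The standard error for one site of 600 is 0.0346, and 2.80 x 0.0346 = 0.097; over 1,800 it is 2.80 x 0.020 = 0.056. So 0.1 matches a per-site calculation for a controlled model in all adolescents. Only the 0.8 is carried forward.

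**Inputs for the check.**
- Tail fraction p = 8-10%, the sample-size text's prevalence of mental health need. This is a proxy; the article does not state the share crossing the thresholds.
- Autocorrelation r = 0.8 from the Analysis plan, with 0.6 as an assumed lower value.
- Correlation between the SDQ at screening and PHQ-9 or GAD-7 at the start of counselling, c = 0.4-0.6 (assumed).
- True counselling effect zero; normal scores.

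**Mean of the selected group.** This is the normal density at the cut divided by p: 1.755 SD above average for the top 10%, and 1.858 SD for the top 8%.

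**Expected fall if the SDQ itself is re-measured**, (1 - r) x selected mean:
- p = 10%: 0.2 x 1.755 = 0.35 SD
- p = 8%: 0.2 x 1.858 = 0.37 SD

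**Expected fall on PHQ-9 or GAD-7**, c x (1 - r) x selected mean:

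| r | lower end (c = 0.4, p = 10%) | upper end (c = 0.6, p = 8%) |
|---|---|---|
| 0.8 | 0.4 x 0.2 x 1.755 = 0.14 SD | 0.6 x 0.2 x 1.858 = 0.22 SD |
| 0.6 | 0.4 x 0.4 x 1.755 = 0.28 SD | 0.6 x 0.4 x 1.858 = 0.45 SD |

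**Where this does not carry over.** BMI is probably very stable, so its regression should be small. The SDQ follow-up questions and the diet items are taken only at 2 and 12 months, so there is no baseline to regress from. Help-seekers below the threshold are not selected on a score.

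**What a comparator would do.** Threshold-positive adolescents in control-condition schools are selected by the same rule at the same assessment. If score distributions and r are similar, their expected regression is the same and cancels in the difference.

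**Rough precision of that comparison.** At 10% positive, each school gives 20. If one school per site crosses first, that is 3 x 20 = 60 against 6 x 20 = 120. Adjusting for the pre-step score, the detectable effect is 2.8 x sqrt(1 - r^2) x sqrt(1/60 + 1/120):
- r = 0.8: 2.8 x 0.600 x 0.158 = 0.27 SD
- r = 0.6: 2.8 x 0.800 x 0.158 = 0.35 SD

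Both ignore school-by-period variation.

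**The case against.** The best defence is that this is meant as description. The article calls it a sub-analysis, heads the section with trajectories rather than effectiveness, warns that causal inference is limited and promises only an initial assessment. It is also a condensed article, and the sub-analysis model may be set out elsewhere. This shows that the overclaim sits mainly in one clause. It does not remove the clause, or the primary question and effectiveness objective that the clause serves.

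A second objection stands in part. The larger figure, 0.35-0.37 SD, is for the SDQ, and the SDQ score is not a Table 2 outcome. PHQ-9 and GAD-7 are first taken at the start of counselling, so their regression is smaller and rests on assumed correlations.

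Two stronger readings are tempting, and the article does not support them:
- **That question 2 would almost certainly be answered yes.** No significance test is specified for this cohort. In simulation with no effect, a before-after t-test on PHQ-9-type outcomes (c = 0.4-0.6, r = 0.6-0.8) showed improvement in about 80-100% of runs for 144-180 pooled adolescents, but in 35-95% for 48-60 at one site. Stable BMI, help-seekers below threshold and items without a baseline weaken the claim further.
- **That the spurious fall is several times the plan's detectable effect.** The 0.1 SD belongs to a controlled model in all adolescents and is no yardstick for before-after change in a selected subgroup.

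It is also fair to object that a comparison between crossed-over and control-condition schools does not isolate counselling. Crossed-over schools also receive health literacy, and control-condition adolescents receive signposting. This limits what the comparison estimates, and the plan should say so.

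**Conclusion.** The point holds. As written, the plan would use uncontrolled change in a group selected mainly by threshold to judge whether counselling works, and it could not separate counselling from regression to the mean, remission, time trend or the concurrent health literacy programme.

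Regression alone is enough to mislead on the mental health scales: about 0.14-0.22 SD on PHQ-9 and GAD-7 at the article's autocorrelation, up to 0.45 SD at 0.6, and about 0.35-0.37 SD on a re-measured SDQ. These sizes depend on the 8-10% proxy, normal scores and, for PHQ-9 and GAD-7, the assumed cross-correlations. Remission, trend and the concurrent programme come in addition and are not quantified here. That the trajectories cannot identify an effect does not depend on any of these numbers.

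**What to change.** 1. Delete the clause about determining whether counselling has an impact, and report the Table 2 trajectories as descriptive.
2. For question 2, add a controlled analysis of SDQ, WHO-5 and BMI. At each step, take adolescents who were threshold-positive at the preceding assessment. Compare those in schools that cross over with those in schools still in the control condition, adjusting for the pre-step score and including site or school and time effects.
3. Define the steps from the actual roll-out schedule at each site. The pattern of one school per site crossing first is inferred here because Figure 2 is not shown, and the article allows site timelines to vary.
4. State that this estimates counselling plus health literacy against signposting, not counselling alone.
5. State that precision is modest: roughly 0.27-0.35 SD at the first step if 10% are positive, one school per site crosses first and there is no school-by-period variation.

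The cost is a change of wording and one additional analysis. No new data are needed, because these measures are already scheduled in all schools and control-condition adolescents with identified problems are already being flagged. If the sponsor does not want the extra analysis, the second primary question should be reworded as descriptive.
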